**Figure 1. F1:**
[figure not shown]
American Academy of Dental Sleep Medicine (AADSM) recommended framework for methods for positioning oral appliance. HRPO: high resolution pulse oximetry; HSAT: home sleep apnea test; PO: pulse oximetry; PSG: polysomnogram.

A total of 60 patients (approximately 6 per dentist) will be enrolled across 10 participating dentists over a 24-month study period, with a planned allocation favoring the enhanced titration approach to support feasibility assessment. Oral appliance therapy is delivered using MADs within routine care, with clinicians retaining discretion over device selection and design features. No protocol-driven training or mandated switching between approaches is imposed, and clinicians continue to follow their usual clinical practices. While this design enhances ecological validity, it may introduce variability related to practitioner and patient factors. These will be addressed analytically through adjustment for measured confounders and the use of generalized estimating equation models to account for clustering of patients within dentists. As a feasibility study, the primary focus is on recruitment, retention, data completeness, protocol adherence, and estimation of preliminary effect sizes to inform future interventional trials. This study protocol is reported using a structured format aligned with STROBE (Strengthening the Reporting of Observational Studies in Epidemiology) guidelines for observational studies [26].

The study is conducted within the STOHN, a regional dental practice–based research network comprising approximately 379 members across private practices, community-based clinics (eg, Federally Qualified Health Centers), and academic or faculty practice settings. Eligible practitioners must meet the following criteria: (1) be a licensed dentist (general dentist or specialist) and a current member of STOHN; (2) be qualified in dental sleep medicine (DSM), as demonstrated through prior training, continuing education, or clinical experience in managing patients with OSA; (3) have treated at least 3 patients with physician-diagnosed OSA using OAT within the past 12 months; (4) complete required human subjects protection training and study-specific training prior to patient enrollment; (5) agree to apply a defined titration approach consistently to all enrolled patients. Dentists from a range of practice settings are eligible, with no restrictions on practice type. Both general dentists and dental specialists may participate. Exclusion criteria for practitioners include participation of more than one dentist from the same practice site to minimize potential inter-dentist contamination.

Dentists from the Southwest Region of the National Dental -PBRN (n=1678) were invited to participate. In addition, the study’s principal investigators encouraged eligible colleagues within the National Dental PBRN, including those outside the Southwest Region, to participate. Eligibility criteria were consistently applied to all invited practitioners.

The study is coordinated by the University of Texas Health Science Center at San Antonio (UTHSA) Clinical Research Informatics/Data Coordinating Center and supported by Clinical and Translational Science Award infrastructure. Participating practices serve as recruitment and data collection sites. Dentist enrollment has been initiated, and patient enrollment is ongoing at the time of manuscript submission. The anticipated study duration is 24 months.

### Study Population

The study population comprises adult patients receiving OAT for OSA in participating dental practices within the STOHN. Eligible participants must meet the following criteria: (1) be aged 18 years or older; (2) have a confirmed diagnosis of OSA established by a qualified sleep physician; (3) have a referral for OAT with a scheduled oral appliance delivery visit at a participating site; (4) be able to communicate in English; (5) have access to email or text messaging for study communication; (6) be willing to complete HSAT using the NightOwl device [16,17]; (7) agree to use an oral appliance embedded with an objective compliance tracker (DentiTrac) [15].

Participants will be excluded if they: (1) lack a physician-confirmed diagnosis of OSA;

(2) have a history of OSA-related surgical treatment (eg, tonsillectomy and/or adenoidectomy or uvulopalatopharyngoplasty [UPPP]); (3) are unable to provide reliable contact information; and (4) decline participation in device-based monitoring. Participants are recruited consecutively from eligible patients receiving routine clinical care at participating sites. The titration approach is determined by the treating practitioner and applied consistently to enrolled patients within each practice.

### Recruitment and Retention

Participating dentists will enroll eligible patients and obtain consent during routine clinical care at the time of dental examination and oral appliance prescription, with consent confirmed at the appliance delivery visit following study onboarding and training. Standardized study materials, including binders with detailed workflow diagrams (Figure 2), data collection guidance, and Research Electronic Data Capture (REDCap; Vanderbilt University) data entry forms, have been developed to support integration of study procedures into routine practice and ensure consistent data collection using REDCap, NightOwl, and DentiTrac devices. An enrollment log is maintained at each site to document screening, eligibility, enrollment, and reasons for nonparticipation.

The study team and STOHN network coordinator provide ongoing support, including protocol guidance, troubleshooting, and monitoring of recruitment progress. Dentist engagement is supported through regular communication, standardized materials, periodic recruitment updates, and continuing education opportunities. Patient retention is facilitated through reminder emails, a text messaging system (short message service, SMS), telephone follow-ups, and flexible scheduling to minimize participant burden and support continued participation.

**Figure 2. F2:**
[figure not shown]
Participant survey distribution workflow. DCC: data coordinating center; EC: exclusion criteria; ESS: Epworth Sleepiness Scale; FOSQ: Functional Outcomes of Sleep Questionnaire; IC: inclusion criteria; PSQ: Patient Satisfaction Questionnaire; RC: research coordinator; REDCap: Research Electronic Data Capture.

### Study Schedule of Assessments

The study includes three study visits conducted during an approximately 8-week titration period (10 days). At visit 1a (screening and consent), eligibility is confirmed, electronic informed consent is obtained, and baseline dental examinations and clinical assessments are completed. At visit 1b (baseline), consent is confirmed, the oral appliance is delivered, baseline questionnaires are administered, and participants initiate HSAT monitoring. Follow-up assessments are conducted. at approximately 4 weeks (visit 2) and 8 weeks (visit 3). At visit 2 (4-week follow-up [10 days]), dentists perform titration adjustments as needed, collect adherence data, and have participants complete follow-up questionnaires and HSAT monitoring. At visit 3 (8-week follow-up [10 days]), final titration is performed if needed, and final adherence data, patient-reported outcomes, and HSAT assessments are collected. Following completion of study procedures, participants return to their sleep physician as part of routine clinical care.

### Data Collection Procedures and Variables

#### Overview

All study data will be collected electronically using a secure REDCap accessible via tablets, smartphones, or computers. Dentist-reported clinical data, patient-reported outcomes, and device-generated measures will be captured using standardized electronic case report forms and integrated data systems. A comprehensive summary of all variables, measurement instruments, variable roles, and data collection time points is provided in Table 1.

**Table 1. T1:** Study variables, measures, and data collection schedule for dentists and patients.

Measurement category	Variable	Variable role^a^	Instrument and source	Time points
Dentists				
Dentist characteristics	Age, sex, years in practice, DSM^b^ training, practice type, referral patterns	Predictor	Dentist demographics form	Baseline
Eligibility	Inclusion and exclusion confirmation	Screening variable	Inclusion and exclusion criteria form	Visit^c^ 1 a
OSA^d^ risk screening	STOP-BANG score	Predictor	STOP-BANG questionnaire	Visit 1 a
Bruxism assessment	Bruxism screening (clinical indicators)	Predictor and clinical assessment	BruxScreen-C questionnaire and dental exam	Visit 1 a
Dental & airway characteristics	Occlusion, range of motion, TMJ^e^ tenderness, airway anatomy	Predictor	Dental examination form	Visit 1 a
Device selection	Appliance type, design features, rationale	Predictor	Device selection form	Visit 1b
OAT^f^ Titration Strategy	Standard versus enhanced titration	Primary Predictor (Exposure)	Device titration form	Visit 1b; Visit 2; Visit 3
Titration characteristics	Mandibular position, advancement increments, and number of adjustments	Predictor	Device titration form	Visit 1b; Visit 2; Visit 3
Clinical symptom monitoring	Snoring, fatigue, and witnessed apneas	Predictor and clinical monitoring	Dentist documentation	Visit 1b; Visit 2; Visit 3
Clinician-observed side effects	Dental discomfort, occlusal changes	Outcome (secondary)	Dentist report	Visit 2; Visit 3
Study participation	Visit completion, withdrawals, protocol deviations	Feasibility Outcome	Study tracking logs	Throughout study
Patients				
Participant characteristics	Age, sex, race and ethnicity, education, income, insurance	Predictor	Patient demographics questionnaire	Visit 1b
Bruxism assessment	Bruxism symptoms and behaviors	Secondary outcome	BruxScreen-Q questionnaire	Visit 1b
Daytime sleepiness	ESS^g^ score	Secondary outcome	Epworth Sleepiness Scale	Visit 1b; Visit 2; Visit 3
Sleep-related quality of life	FOSQ-10^h^ score	Secondary outcome	FOSQ-10 questionnaire	Visit 1b; Visit 2; Visit 3
Patient satisfaction	Satisfaction with dental sleep care	Secondary outcome	PSQ-18^i^	Visit 3
Patient-reported side effects	Jaw pain, tooth discomfort, bite changes	Secondary outcome	Sleep and Side effects questionnaire	Visit 1b; Visit 2; Visit 3
Physiologic sleep measures	AHI^j^, RDI^k^, SpO2 nadir, time <90% oxygen saturation	Primary outcome Component	NightOwlHSAT^l^	Visit 1b; Visit 2; Visit 3
Objective adherence	Hours of nightly oral appliance use; head position	Primary outcome component	DentiTrac compliance tracker	Continuous; summarized at Visit 2 and Visit 3
Treatment effectiveness	MDA^m^	Primary outcome	Derived (AHI × adherence)	Visit 2; Visit 3
Patient experience	Perceived benefit, willingness to continue therapy	Exploratory outcome	Patient questionnaire	Visit 3

a Variable roles: predictor variables represent dentist, patient, or clinical characteristics that may influence treatment outcomes. Outcome variables include patient-reported outcomes, clinician-observed effects, feasibility indicators, and the primary effectiveness outcome. Physiologic sleep measures and objective adherence data are combined to derive the primary outcome MDA, calculated as treatment efficacy (change in AHI measured by NightOwl HSAT) multiplied by objective adherence (hours of nightly oral appliance use recorded by the DentiTrac compliance micro tracker).

b DSM: dental sleep medicine.

c Visit definitions: Visit 1a = eligibility screening, consent, and baseline dental examination/clinical assessment; Visit 1b = oral appliance delivery and baseline questionnaires; Visit 2 and Visit 3 = follow-up visits during the titration period.

d OSA: obstructive sleep apnea.

e TMJ: temporomandibular joint disorder.

f OAT: oral appliance therapy.

g ESS: Epworth Sleepiness Scale.

h FOSQ: Functional Outcomes of Sleep Questionnaire.

i PSQ-18: Patient Satisfaction Questionnaire.

j AHI: apnea–hypopnea index.

k RDI: respiratory disturbance index.

l HSAT: home sleep apnea test.

m MDA: mean disease alleviation.

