**Methods:**

This prospective, multisite, observational feasibility study will enroll approximately 60 adult patients with physician-diagnosed obstructive sleep apnea receiving OAT from 10 dental practitioners within the South Texas Oral Health Network, with each practitioner enrolling up to 6 patients. Practitioners will apply either standard signs-and-symptoms–based titration or enhanced multimethod positioning titration, as per their usual clinical practice. Clinical, dental, and titration characteristics will be collected at baseline and follow-up visits over an approximately 8-week titration period. The primary outcome is mean disease alleviation, calculated as the product of physiologic efficacy (change in apnea–hypopnea index derived from multinight home sleep apnea testing) and objective adherence (hours of nightly oral appliance use captured via an embedded compliance tracker). Secondary outcomes include daytime sleepiness, sleep-related quality of life, patient satisfaction, oral appliance–related side effects, and bruxism. Descriptive analyses and generalized estimating equation models will be used to account for clustering of patients within practitioners.

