Traditional measures of OAT effectiveness have focused on reductions in the apnea–hypopnea index (AHI); however, AHI alone does not reflect real-world treatment benefit because adherence to therapy varies substantially across patients. Objective compliance monitoring using embedded micro trackers enables precise quantification of nightly appliance use and calculation of mean disease alleviation (MDA), which integrates both treatment efficacy (AHI reduction) and adherence [7,10]. MDA is now recognized as a superior measure of therapeutic effectiveness for OAT [7,10,14]. Advances in digital health technologies now enable the integration of objective physiologic and adherence data in routine clinical practice. The DentiTrac tracker provides objective adherence data [15], while multinight HSAT, for example, NightOwl, provides physiologic measures of sleep-disordered breathing as an alternative to polysomnography in appropriately selected patients [16-18]. Together, these tools allow for more precise and scalable evaluation of treatment effectiveness in real-world settings.

Most studies evaluating OAT titration have been conducted in academic or specialty sleep centers, limiting their generalizability to real-world dental practice. Practice-based research networks (PBRNs) offer a validated infrastructure for studying care delivery in real-world clinical environments [19-21]. The South Texas Oral Health Network (STOHN) PBRN [22,23], in collaboration with the National Dental Practice-Based Research Network (PBRN) [19-21,24], serves a highly diverse patient population, including large Hispanic, publicly insured, and uninsured communities, providing a uniquely representative setting for evaluating OSA care. Dental PBRNs facilitate the study of clinically relevant questions by integrating research into routine practice. A 2021 National Dental PBRN survey of 311 dental practitioners (general dentists and specialists) found that titration, patient compliance, and management of side effects were among the most important and least understood aspects of dental sleep medicine practice [25]. These findings highlight a critical need for practice-based, objective evidence to guide OAT titration.

The primary objective is to evaluate the feasibility and preliminary comparative effectiveness of two oral appliance therapy (OAT) titration approaches, standard signs-and-symptoms–based titration and enhanced multimethod positioning as implemented in routine clinical practice.

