#### Objective Physiologic and Adherence Measures

Physiologic sleep measures are obtained using the NightOwl HSAT device, with assessments conducted at baseline and follow-up visits as specified in Table 1. Objective adherence is measured using the DentiTrac compliance tracker embedded within the oral appliance, which records nightly usage duration and head position. Adherence data are collected continuously and summarized at follow-up visits.

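### MDA multiplies the AHI change by raw hours of appliance use with no sleep-time denominator, so it cannot be read as the proportion of disease alleviated

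*Protocol article*

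**What the plan says.** The Methods paragraph of the Abstract gives the second factor of MDA as "objective adherence (hours of nightly oral appliance use captured via an embedded compliance tracker". Footnote a to Table 1 repeats this. There the efficacy term is the AHI change on the home sleep test, and that term is "multiplied by objective adherence (hours of nightly oral appliance use recorded by the DentiTrac compliance micro tracker". The MDA row of the table is shorter still, "Derived (AHI × adherence", and has no third term.

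The inputs listed in Table 1 are:
- from the home sleep test: "AHI^j^, RDI^k^, SpO2 nadir, time <90% oxygen saturation";
- from the tracker: "Hours of nightly oral appliance use; head position". The section Objective Physiologic and Adherence Measures agrees, describing a device "which records nightly usage duration and head position".

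The questionnaire with sleep in its title is listed only for jaw pain, tooth discomfort and bite changes. Total sleep time, recording time and self-reported sleep duration are not listed, and nothing restricts tracker hours to time asleep. The Overview presents Table 1 as covering all variables. The Introduction describes MDA as a measure "which integrates both treatment efficacy (AHI reduction) and adherence" and treats it as a measure of therapeutic effectiveness.

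**The concern.** AHI is an hourly rate that applies to sleep. To say how much of a patient's disease was alleviated, one needs the share of sleep during which the appliance was worn. Raw hours do not give that share. Two patients can wear the appliance equally long, one covering the whole night and the other leaving hours of sleep untreated. Hours worn while awake count as benefit although they avert no sleep events.

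Two things are at stake. The first is interpretation: the outcome's name and the Introduction suggest a measure of how much disease was removed, and the product does not give it. The second is the effect size carried forward. The section Study Design and Setting makes estimation of preliminary effect sizes part of the study's main focus, and Sample Size says the sample is meant to estimate the variability of MDA. Variation in habitual sleep length enters that variability. The comparison is also nonrandomized, and sleep duration is neither a listed variable nor a named confounder in the Statistical Analysis Plan section.

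**Working it through.** **The plan's own figure.** The only number the article gives for MDA is the detectable standardized difference of about 0.82 to 0.97 (Sample Size). Use d = (1.96 + 0.84) × √[1/(Ne·p) + 1/(Ne·(1−p))], with Ne = 60 / [1 + (6−1)·ICC].
- ICC 0.05, allocation 4:6: Ne = 60/1.25 = 48, arms 19.2 and 28.8, d = 0.825.
- ICC 0.10, allocation 3:7: Ne = 60/1.5 = 40, arms 12 and 28, d = 0.967.

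This matches with all 60 patients evaluable. How attrition enters is a separate matter. The figure is in standard deviation units, so it neither supports nor contradicts the present point.

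**Units.** Change in AHI (events/h) × hours = events per night, and this holds only if the hours are hours of sleep. A coverage measure is change in AHI × (hours worn asleep / hours asleep). It becomes a proportion of disease if the AHI change is also taken relative to baseline. The article does not say whether the change is absolute or relative. The missing denominator arises either way.

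**Illustration.** The documents give no sleep or wear times, so all inputs here are assumed: AHI 30 falling to 10 (reduction 20/h, or 66.7%), sleep 5.5 to 9 h, wear 5.5 to 9 h.

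| Sleep (h) | Worn (h) | As written: 20 × worn | Coverage, capped at 1 | 66.7% × coverage |
|---|---|---|---|---|
| 5.5 | 5.5 | 110 | 100% | 66.7% |
| 8 | 5.5 | 110 | 69% | 45.8% |
| 8 | 8 | 160 | 100% | 66.7% |
| 6 | 6 | 120 | 100% | 66.7% |
| 9 | 6 | 120 | 67% | 44.4% |
| 9 | 9 | 180 | 100% | 66.7% |
| 6 | 7.5 (1.5 awake) | 150 | 100% | 66.7% |

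- Same score, different coverage: 110 for both 100% and 69%.
- Same coverage, different score: 110 and 160 (160/110 = 1.45), or 120 and 180 (1.50).
- Awake wear of 1.5 h raises the score from 120 to 150, which is 25%.

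**Effect on spread.** Assume everyone wears the appliance all night and sleep has mean 7 h and SD 1 h. The hours factor then has a CV of 1/7 = 14%, where the coverage share would have none. If the two factors are independent, CV² of the product = (1 + 0.143²)(1 + c²) − 1, with c the CV of the AHI change.
- c = 40%: 42.9%, a rise of about 7%.
- c = 60%: 62.3%, a rise of about 4%.
- c = 80%: 82.1%, a rise of about 3%.

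**Limit of a capped ratio.** A patient who sleeps 6 h, wears the appliance 1.5 h awake and removes it 1.5 h before waking has 6 h on the tracker. The capped ratio is 6/6 = 1, while true coverage is 4.5/6 = 75%.

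**The case against.** The strongest reply is that the product is coherent as events averted per night. On that scale 160 against 110 is correct, because a patient treated through 8 h of sleep does avert more events than one treated through 5.5 h. The two patients scoring 110 do avert the same number, and only their residual burden differs. This stands. Choosing a count over a share is a choice of target quantity, and the article nowhere defines MDA as a percentage. Awake wear is the one feature mis-scored on both readings, and the documents do not say how common it is.

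Second, the article condenses a fuller protocol and cites MDA as an existing measure, so scaling could be set out elsewhere. That carries some weight. But footnote a and the Abstract both state the factor in hours, and the Overview describes Table 1 as comprehensive, so this is a stated rule and not a detail left open.

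Third, a reader might infer that sleep duration is not collected at all. The documents do not support that. An hourly index needs a time base, and Data Management and Monitoring says NightOwl data are centralized. What can be said is that no duration is listed in Table 1 or used in MDA.

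Fourth, the effect on spread is small beside plausible variation in the AHI change, and a ratio built on a few test nights brings error of its own. Both are fair, and they limit how strongly the point can be put.

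**Conclusion.** The point holds as one of definition. As written, MDA is at best events averted per night. It credits awake wear and cannot separate full from partial coverage of sleep, so it cannot be read as the proportion of disease alleviated.

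Its numerical size is not known. The illustrations rest on assumed sleep and wear times. The 14% CV further assumes full wear by everyone, and it becomes a 3% to 7% rise in the CV of MDA only under an assumed CV of 40% to 80% for the AHI change and independent factors.

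A reader might go further and conclude that the comparison of titration approaches is biased. That needs sleep length or awake wear to differ between the approaches, and nothing in the article shows this. Otherwise the consequence is added variance and a score that is hard to interpret. The change should be made before analysis, but the point does not undermine the feasibility aims.

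**What to change.** - Add sleep time from the existing NightOwl recordings to Table 1, with valid recording time only as a fallback if sleep time is not reported.
- Define the adherence factor as DentiTrac hours divided by that sleep time, capped at 1. State the units of MDA, including whether the AHI change is absolute or relative to baseline.
- Keep the raw-hours product as a secondary or sensitivity measure, labelled as events averted per night.

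The cost is one listed field and one derivation line, with no new test or visit. Recruitment is projected to run through January 2027 with analysis afterwards, so there is time. If the full protocol already scales the hours, only the article's definition and Table 1 need correcting.

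Two downsides should be stated in the plan. Sleep time from the test nights stands in for all the other tracker nights, and the cap removes awake wear only in part. Where recording time is the fallback, the ratio is no longer strictly a share of sleep.
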